#### Decision-making regarding patient management

Patients will be discussed at the local multidisciplinary meeting (standard care) and decisions regarding the management of the patient including the need for additional radical surgical resection or other treatment options, will be made there in the normal way in accordance with the current national guidelines.

#### Follow-up

The follow-up consists of a rectoscopy performed 6 and 12 months after the TAMIS/ESD by an endoscopist trained in advanced endoscopic imaging techniques. Three white light pictures, 3 enchanced imaging pictures and preferably a short video should be taken of the scar. In case of no visible recurrence 3 biopsies of the scar should be taken. In case of visible benign recurrence an attempt at an endoscopic resection will be performed, or a re-TAMIS. If recurrence is found at the 12-month rectoscopy this will be resected and further surveillance will be planned for 6 months later.

### Informed consent procedure

Patients meeting all criteria stated above will be informed about the trial at the outpatient clinic by a member of the research team. After written consent is obtained the patient will be allocated to either the TAMIS or the ESD group by computerised randomisation. Subsequently, the patient will be scheduled for therapy at a participating centre.

### Intervention failure: cross-over

If the primary procedure fails, cross-over to the other treatment is possible, but only if the specialist that has to perform the cross-over treatment, deems it feasible.

### Quality assurance

#### Expert panel

An expert panel was established for this trial consisting of five gastroenterologists (JH, JB, LM, AK, BB) and three surgeons (PD, EG, RH). All are specialized in the assessment and treatment of advanced polyps and (early invasive) rectal cancers and perform either the ESD or the TAMIS procedures within this trial. All lesions should be approved by the expert panel before randomisation by review of the endoscopy pictures and video. A lesion is deemed as suitable for participation if a minimum of 2 gastroenterologists and 1 surgeon think the lesion meets the criteria. The expert panel can also be consulted in difficult cases (for example when advanced cross-sectional imaging and endoscopic assessment disagree).

#### Experience requirement

Specialists performing ESD or TAMIS in the TRIASSIC study need to have performed at least 25 procedures. The specialists will be asked to send anonymised procedural data including lesion characteristics, procedure time, complications, histology and follow up (if available) of the latest 15 procedures and an unedited video. To be able to perform procedures in the TRIASSIC study at least 10 of these 15 procedures must have resulted in a R0 resection of lesions > 2 cm in size and must have been performed without complications.

### Histopathological evaluation

Appropriate handling of the resected specimens is critical for accurate histological assessment and will be done as follows (identical to standard care). The resected specimen will be pinned onto a paraffin, rubber or cork sheet so that the normal mucosa surrounding the lesion is evenly flattened and the mucosal surface can be observed. The specimen will then be photographed with a millimetre ruler next to it and fixed in formalin. The specimen should, preferably, be examined by a GI pathologist. The specimen should be photographed, measured and macroscopic appearance described including the lesion, mucosal defects, other abnormalities and the resection margins. The specimen should also be inked. A different colour should be used for the resection plane and the edges of defects. A tangent that touches the focus closes to the horizontal margin is assumed. The first cut is carried out in the direction perpendicular to the tangent. Hereafter the specimen is sectioned into slices parallel to the first cut. Lastly all slices should be embedded in cassettes for histological diagnosis. Incomplete (R1) resection is defined as tumour infiltration of the margins and/or if infiltration cannot be determined because of coagulation artefacts. In case of an adenocarcinoma the high-risk factors will be assessed; grade of tumour budding, invasion depth, differentiation grade, presence of lymphovascular invasion and radicality.

#### Central pathology revision

All resection specimens will be revised centrally by an expert pathologist.

### Outcomes

#### Primary study endpoint (for non-inferiority)

Cumulative recurrence rate at follow-up rectoscopy after 12 months, histologically confirmed from resected visible residual disease or, if not present, from biopsies of the scar

#### Secondary study endpoints

2.Radical (R0-) resection rate, defined as dysplasia-free vertical and lateral resection margins at histology3.To compare the perceived burden of the treatment and quality of life among patients using questionnaires ((EORTC) QLQ-C29 [12], EUROQOL EQ-5D-5L [13], COREFO [14]).4.Overall complication rate*5.Surgical referral rate defined as the number of patients that are referred for trans-abdominal surgical management at 12 months6.Cost effectiveness at 12 months.

#### * complications are defined as follows

*Intraprocedural peritoneal breach: the condition in which the abdominal cavity is visible from the colorectal lumen during the procedure because of mural tissue defects, that requires* (1) *(prolonged) admission or* (2) *surgery**Intraprocedural bleeding: bleeding that occurs during the procedure that cannot be controlled by standard local haemostasis techniques such as electrocoagulation or clips and that requires* (1) *transfusion or* (2) *termination of the TAMIS or ESD procedure.**Postprocedural bleeding: bleeding within 30 days after the procedure resulting in* (1) *new presentation at the hospital,* (2) *hospital admission, transfusion* (3) *or* (4) *repeated intervention to obtain haemostasis.**Postprocedural bowel perforation: a bowel perforation within 30 days after the procedure that is detected after completion of the procedure during which a peritoneal breach did not occur, diagnosed by abdominal pain with focal guarding and a rise in C-reactive protein and/or fever (T > 38.5 C) in combination with free air in the peritoneal cavity at abdominal CT.**Postprocedural serositis: abdominal pain with focal guarding and/or fever (T > 38.5 C) within 30 days after the procedure, but without signs of perforation (free air at abdominal CT) and in the absence of another infection focus (urinary, pulmonary* etcetera*) that requires (prolonged) admission*

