Ideally, preoperative staging would allow for accurate prediction of invasive cancer and the chance of local lymph node metastases. Unfortunately, current preoperative staging is far from perfect. This is true for all available staging modalities (MRI, endoscopic ultrasound, advanced optical endoscopic imaging) both individually and in combination. This has been shown by a previous randomised study of organ sparing treatment of rectal polyps, the TREND study: 13% of the lesions preoperatively staged as benign turned out to be malignant [5]. Currently most lesions that are not overtly cancerous on endoscopic inspection are resected by piecemeal Endoscopic Mucosal Resection (pEMR) in Western countries. However, piecemeal resection has an important disadvantage in that it prevents optimal histological assessment. This can make histological distinction between a benign and a malignant lesion impossible leading to unnecessary surgical resections or to under staging and undertreatment. The safety and feasibility of *en bloc* resections in the rectum, combined with the limitations of preoperative staging are leading to a shift away from pEMR to *en bloc* resection of large lesions in the rectum. Furthermore, a recent cost-effectiveness analysis suggests that an *en bloc* resection strategy might also be cheaper than a piecemeal resection strategy for rectal lesions by reducing the numbers of patients requiring additional radical rectal surgery [6].

Lesions can be removed *en bloc* with a flexible endoscope by Endoscopic Submucosal Dissection (ESD). ESD results in high *en bloc* rates and low recurrence rates of around 2% [7]. However, ESD has longer procedure times, is difficult to perform and associated with relatively high rates of perforation (5%) [8]. Fortunately, the clinical consequences of perforation in the rectum are usually limited and can almost always be treated conservatively. Several surgical techniques are also available for local *en bloc* resection of large non-pedunculated rectal lesions. Such as Transanal Endoscopic Micosurgery (TEM) or Transanal Minimally Invasive Surgery (TAMIS). The TAMIS technique has largely superseded classical TEM since it requires minimal investment in specialised equipment. Here the lesion is removed transanally with the use of a silicon-rubber port and standard laparoscopic instruments. Compared to ESD it also has a relatively short learning curve, short procedure times and is financially well compensated.

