### Intervention strategies

#### Transanal minimally invasive surgery (TAMIS)

This procedure was first described by Atallah et al. [11]. The procedure will be performed under either general or spinal anaesthesia at the discretion of the anaesthetist. For this trial only the GelPOINT® path transanal access platform will be used. This is to ensure the greatest possible uniformity in procedures and was already being used by the vast majority of surgeons prior to the study. After insertion of the instruments the margins of the lesion may be marked with coagulation dots to facilitate the incision at the lesion margins at the discretion of the surgeon. The incision must be placed at a distance of at least 5 mm around the border of the lesion to prevent thermal damage complicating the histological assessment. If a lesion is very distal (i.e., at or just above the dentate line), the distal margin can be incised using standard transanal retractors and electrocautery. Before the start of the lateral or proximal portion of the dissection, the TAMIS port can be inserted to be used for the remainder of the dissection. Ideally a partial thickness resection of the lesion will be performed following the intramuscular plane of the muscularis propria using a diathermic hook but a full thickness resection may be performed at the discretion of the surgeon. The wound may be closed, if required, with laparoscopic suture material in a transverse direction so as not to narrow the lumen of the rectum. The type of sedation and precise instruments will be noted in the CRF. Pneumorectum will be achieved using CO2 for insufflation. Initial pressure settings should be between 12- and 20-mmHg and can be increased if there is difficulty in maintaining distension for visualisation. An anal block with bupivacaine or ropivacaine bilaterally is recommended. All other aspects of the procedure and post-procedural care are at the discretion of the operator.

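### A symptomatic extraperitoneal perforation or leak can never be classed as a perforation; it is either uncounted or recorded as serositis, depending on how free air is read

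*Protocol article*

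**What the plan says.** Overall complication rate is a secondary endpoint (Protocol article, Secondary study endpoints). The text below it defines complications as five categories: intraprocedural peritoneal breach, intraprocedural bleeding, postprocedural bleeding, postprocedural bowel perforation and postprocedural serositis. There is no category for other events.

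Three of the five could capture a defect of the rectal wall:

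- **Intraprocedural breach** requires that the abdominal cavity could be seen from inside the bowel, and that admission (or a longer stay) or surgery followed.
- **Postprocedural perforation** is "diagnosed by abdominal pain with focal guarding and a rise in C-reactive protein and/or fever", "in combination with free air in the peritoneal cavity at abdominal CT". It must also be "detected after completion of the procedure during which a peritoneal breach did not occur".
- **Postprocedural serositis** is guarding and/or fever that requires admission or a longer stay, "but without signs of perforation (free air at abdominal CT) and in the absence of another infection focus".

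Distal lesions are expected. Eligibility covers lesions whose bulk lies below 15 cm from the anal verge, the TAMIS section provides for lesions at or just above the dentate line, and randomisation is stratified by distance to that line. TAMIS may be full thickness at the surgeon's discretion, whereas ESD stays in the submucosa. The Hypothesis section expects fewer serious complications with ESD, and the Background gives a perforation rate of 5% for ESD.

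**The concern.** The perforation definition says where the air must be. The serositis definition, which should be its complement, does not. A low rectal wall defect may open into the tissue beside the rectum and leave no air in the peritoneal cavity. Such a patient cannot be a perforation, and whether the patient is a serositis case depends on how the person classifying the event reads free air. The trial is unblinded, so a safety category that turns on interpretation is undesirable.

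At stake is the complication comparison. On one reading true events leave the overall rate. On the other they stay in it but are listed as serositis, so the perforation count is too low. Resection depth differs between the arms by design, so the events missed or mislabelled need not be equally frequent in both.

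**Working it through.** No published figure is to be reproduced; the check is of the logic. The test case is a postprocedural perforation or leak with extraperitoneal air only on CT, no intraprocedural breach and no other infection focus.

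**Inputs** (all from the complication definitions): guarding G, fever F, C-reactive protein rise C, admission A, each yes or no. That gives 2 × 2 × 2 × 2 = 16 combinations.

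**Rules as written**

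- Perforation = G and (C or F) and intraperitoneal air.
- Serositis = (G or F) and A and no free air.

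**Perforation.** The clinical part is met in 1 × 3 × 2 = 6 combinations (guarding present; 3 of the 4 pairs of C and F; A either way). The air condition fails in all of them, so the result is 0 of 16.

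**Serositis.** The clinical part with admission is met in 3 × 2 × 1 = 6 combinations (3 of the 4 pairs of G and F; C either way; A present). The result then depends on the reading of free air:

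| Reading of free air in the serositis definition | Perforation | Serositis | Outcome |
|---|---|---|---|
| Air in any compartment (literal wording) | 0 of 16 | 0 of 16 | Never counted |
| Intraperitoneal air only | 0 of 16 | 6 of 16 | Counted as serositis in 6, uncounted in 10 |

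The 10 are the 8 combinations without admission plus the 2 with admission but neither guarding nor fever.

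Take only the 6 combinations that carry the full clinical picture of the perforation definition. On the narrow reading, the 3 with admission become serositis and the 3 without are uncounted. Intraperitoneal air with the same signs would count as perforation in all 6, because that definition does not require admission. These counts describe the logic of the rules; the combinations are not equally likely.

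**Related cases**

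- A collection without free air passes the serositis CT condition on either reading. It is then serositis unless the collection is held to be another infection focus.
- A wall defect found at re-intervention without CT cannot be a postprocedural perforation, because the CT sign is required.
- A delayed perforation after a peritoneal breach is barred from the perforation category. If the breach required admission or surgery, the patient is already in the overall rate, so only the category count suffers.

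**Size.** Each patient who drops out of the count changes that arm's complication rate by 1/99 = 1.0 percentage point. How many would do so is not derivable: the document gives neither the share of lesions below the peritoneal reflection nor the share of perforations with extraperitoneal air only.

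**The case against.** Several objections have weight.

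- **The overall rate may be unaffected.** If free air means intraperitoneal air throughout, an admitted patient with guarding or fever counts as serositis and the endpoint total does not change. This stands for that reading. A reader might infer that both definitions recognise intraperitoneal air only and that the case is therefore always lost. The text does not support this: only the perforation definition names the compartment, and reading both that way is what brings the admitted case back in as serositis.
- **No number of lost events can be given.** A reader might multiply the Background's 5% by 99 to get 4.95 ESD patients, and then by an assumed 30–70% of lesions below the peritoneum to get 1.5–3.5. The document does not support this. The 5% is not split by timing or compartment, the 30–70% is not in the document, and an intraprocedural breach that needs neither admission nor surgery is left out at any height.
- **A pelvic abscess is not clearly another focus.** The examples given are urinary and pulmonary, which are unrelated to the resection site. Treating an abscess at that site as a disqualifying focus is a strained reading.
- **Lesion height is balanced.** Stratification by distance to the dentate line balances where lesions lie, so no direction of bias is shown. This stands, although balance in height does not make the two procedures equally likely to cause such events.
- **A peritoneal criterion has a purpose.** After full-thickness TAMIS, air outside the bowel wall may be expected. A criterion of any extraluminal air could relabel a febrile TAMIS patient as a leak. This stands and shapes the fix.
- **Events are recorded elsewhere, and an article condenses the protocol.** Management of ESD perforation goes into the CRF and healthcare use is collected. But the definitions are stated in the article and do not match each other, so this is not a detail left to the full protocol.

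**Conclusion.** The point holds in limited form. The two postprocedural definitions use different wording for the same sign, and the list has no residual category. A symptomatic perforation or leak with only extraperitoneal air can therefore never be classed as a perforation. On the literal reading it is uncounted; on the narrow reading it is recorded as serositis if the patient is admitted with guarding or fever, and is otherwise uncounted.

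The conclusion assumes that some distal wall defects open outside the peritoneal cavity and that the five categories are applied as written. The number of patients and the direction of any effect between arms are unknown. The clause on a preceding breach mostly affects category counts.

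The effect is confined to the secondary complication endpoint and the hypothesis of fewer serious complications with ESD. The primary endpoint, the 166 evaluable patients and the total of 198 rest on recurrence alone and do not change. The definitions should be reconciled because this is cheap and the events concerned are central to the safety comparison.

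**What to change.** Amend the endpoint definitions as follows, identically for both arms:

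- State the compartment of the air in the same words in the perforation and serositis definitions.
- Add a listed subcategory for symptomatic extraperitoneal perforation or leak: clinical signs within 30 days plus extraperitoneal air or a collection on CT, or a wall defect found at re-intervention. Report it separately from intraperitoneal perforation, because full-thickness TAMIS may leave expected extraluminal air.
- Make serositis the residual category: admitted patients with guarding or fever who do not meet the perforation or leak definition.
- Drop the bar on perforation after a breach. Count a patient with both events once in the overall rate and list both.

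The cost is revised wording and one CRF item for the location of air or a collection; no extra imaging is needed. The downside is a slightly higher reported complication rate that may not rise equally in the two arms, which is why the new subcategory must be shown separately.

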### Sample size calculation

The sample size was calculated for the primary outcome parameter, the cumulative recurrence rate at 12 months. To assess the non-inferiority of the ESD procedure the sample size calculation was based on the assumption that the recurrence rate will be 3% in the ESD group and 6% in the TAMIS group based on a systematic review of the literature specifically for studies performed in the West. If there is a true difference in favour of ESD of 3%, then 166 patients are required to be 80% sure that the upper limit of a one-sided 97.5% confidence interval (or equivalently a 95% two-sided confidence interval) will exclude a difference in favour of the TAMIS of more than 6%. (Software: PASS Version 15 – www.ncss.com). We have chosen a non-inferiority margin of 6% because we believe that this difference in risk of benign recurrence between the intervention group and usual care group is clinically acceptable. To allow for patients lost to follow-up (4%) and patients requiring additional surgical resection due to high risk characteristics (12%) in whom the primary outcome cannot be assessed, a total of 198 patients will be included; 99 patients in each arm. The incidence of large rectal non-pedunculated lesions in the Netherlands is estimated to be between 250 and 500 new cases a year. We estimated that the participation of 15 centres will be required to complete the inclusion period within 3 years. To avoid unnecessary delay, we will start this trial with 5 centres and will extend the number of centres during the course of the trial.

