No reports have been published comparing TAMIS and ESD directly. Two recently published meta-analysis comparing TAMIS/TEM to ESD concluded a similar rate of adverse events, recurrence rate and *en bloc* resection rate [9, 10]. Regarding the procedure and hospitalization duration both papers came to a different conclusion. The first concluded that ESD was associated with shorter procedure times and duration of hospitalization [10], the second concluded that there was no difference [9]. However, both meta-analyses largely included ESD procedures that were conducted in Asian countries. As a result the findings may not be representative for the daily practice in the West where the results of ESD tend to be inferior. The aim of the TRIASSIC study is to perform a multicentre, randomised controlled study comparing ESD to TAMIS for the *en bloc* removal of large non-pedunculated rectal lesions in a Western population. This is important as the detection rate of these lesions has increased greatly with the introduction of screening programs. This study will enable the optimal use of healthcare resources in the future.

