### Data-analysis

To assess the non-inferiority of the ESD procedure, the difference between the cumulative recurrence rates at 12 months in both groups will be compared to the non-inferiority margin of 3% using a one-sided Mantel-Haenszel test (with alpha 0.025) to account for stratification factors. For the other variables, normality will firstly be assessed. The secondary endpoints will be compared using the student t-test or Mann-Whitney U test and Chi-square or Fisher’s exact test as appropriate. Multivariate regression will be considered for adjustment for possible confounding if necessary. The analysis will primarily be carried out on an intention-to-treat basis.

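### The sample size section's 80% power and one-sided 2.5% error do not hold together at about 2.5 and 5 expected recurrences; an interval that keeps the error near 2.5% has about 73% power

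*Protocol article*

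**What the plan says.** The Sample size calculation assumes that "the recurrence rate will be 3% in the ESD group and 6% in the TAMIS group", taken from a systematic review of Western studies. It makes the power conditional on that 3-point advantage for ESD: "then 166 patients are required to be 80% sure that the upper limit of a one-sided 97.5% confidence interval" will exclude a TAMIS advantage larger than the margin. The interval is described further as "or equivalently a 95% two-sided confidence interval", so the intended one-sided error is 2.5%. The margin in this section is 6 percentage points. PASS 15 is cited, but the formula or test option is not named. The 166 is raised to 198 (99 per arm) for 4% lost to follow-up and 12% who need further surgery and so have no assessable outcome.

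The Data-analysis section plans a one-sided Mantel-Haenszel test at alpha 0.025 that accounts for the stratification factors, but against a margin of 3%.

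**The concern.** The section attaches two properties to one sample size: 80% power and a one-sided error of 2.5%. With 83 patients per arm and recurrence of 3% and 6%, the comparison rests on a handful of events. Normal-approximation intervals for a difference in proportions are unreliable there. They tend to be too narrow on the side that matters for non-inferiority, which raises the apparent power and the false-positive risk together.

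Two things are at stake. If the analysis uses a Wald-type interval, ESD could be declared non-inferior with more than the stated risk of error. If it uses an interval that controls the error, the trial has less power than readers are told, and a missed margin is harder to interpret.

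**Working it through.** **Inputs** (all from the Sample size calculation): recurrence 3% (ESD) and 6% (TAMIS); margin 6 points; one-sided alpha 0.025; power 80%; 166 evaluable patients, 83 per arm; 16% without an assessable outcome.

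**1. Reproduce the plan's figures.** Unpooled normal formula:

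n per arm = (1.960 + 0.842)² × [0.03 × 0.97 + 0.06 × 0.94] / (0.06 + 0.03)²
= 7.849 × 0.0855 / 0.0081 = 82.85, so 83 per arm and 166 in total. The approximate power at 83 per arm is 80.07%.

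166 / (1 − 0.16) = 197.6, so 198. Both stated figures are reproduced.

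Other formulas, same inputs:

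| Formula | n per arm |
|---|---|
| Unpooled normal | 82.85 → 83 |
| Pooled-variance normal | 83.2 to 83.3 → 84 |
| Continuity-corrected | 104 |
| Farrington-Manning score, normal approximation | 106 |

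Use of a plain large-sample formula is therefore inferred from the match; the article does not name it.

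**2. Expected events.** 83 × 0.03 = 2.49 with ESD; 83 × 0.06 = 4.98 with TAMIS.

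**3. Exact behaviour at 83 per arm, margin 6 points.** Every pair of event counts is enumerated with its binomial probability, and the pairs whose upper limit lies below 6 points are summed.

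| True rates (ESD / TAMIS) | Meaning | Wald | Score (Farrington-Manning) |
|---|---|---|---|
| 3% / 6% | power at the design assumption | 82.8% | 73.4% |
| 12% / 6% | error, TAMIS at its design rate | 3.0% | 2.3% |
| 9% / 3% | error, TAMIS rate lower | 4.2% | 2.1% |
| 6% / 6% | power if recurrence is equal | 40% | 32% |
| 3% / 3% | power if recurrence is equal | 66% | 44% |

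Miettinen-Nurminen and Newcombe intervals also have 73.4% power at 3% / 6%. Over TAMIS rates of 1% to 15%, the largest error of the Farrington-Manning and Newcombe methods is about 2.5%. An exact unconditional score test that holds 2.5% over all TAMIS rates has 69.5% power.

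**4. The planned stratified analysis.** A stratified Mantel-Haenszel risk difference with Sato variance was simulated with 200,000 runs and four equal strata (an assumption). Power was 81.9%, with an error of 3.2% at 12% / 6% and 4.1% at 9% / 3%. It behaves like the Wald interval: it reaches the power but exceeds the alpha.

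**The case against.** The strongest reply is that nothing has been miscalculated, and that 73% belongs to a score method the article never names. With an interval that matches the formula, or with a Wald-type Mantel-Haenszel analysis, exact or simulated power is 82% to 83%. The error at the design's own null (12% against 6%) is then only 0.5 to 0.7 points above nominal; the 4.2% needs a TAMIS rate of 3%, which is not the design assumption. All of this stands, and it limits the size of the point. It does not remove it: the section states the error level as well as the power, and none of the methods examined delivers both.

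Three stronger readings are tempting but unsupported.

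- A reader might infer that 166 or 198 is an arithmetic slip. Both reproduce.
- A reader might infer that the Background contradicts the assumed rates, because it says two meta-analyses "concluded a similar rate of adverse events, recurrence rate" and speaks of practice "in the West where the results of ESD tend to be inferior". Those meta-analyses compared TAMIS/TEM with ESD and drew largely on Asian ESD series, which the same section says may not be representative. The second remark concerns ESD results in general, not recurrence. The 3% and 6% are attributed to a review of Western studies that is not shown. The documents do not establish that the assumption is wrong.
- A reader might infer that the dependence on a true ESD advantage is hidden. It is stated openly, and powering on a stated favourable alternative is a legitimate choice. The equal-rates figures show how sensitive the design is; they are not evidence of an error.

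It can also be said that the conflict between margins is the larger problem. It is a separate one: with a 3-point margin, the plan's own formula gives about 46% power at 83 per arm. The figures here take the 6-point margin, the reading more favourable to the plan.

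**Conclusion.** The point holds, at moderate size. With 166 evaluable patients the design does not have 80% power and a 2.5% one-sided error together. Power is about 73% under a score-type interval (69.5% under a strict exact test), some 7 points below the stated figure. Alternatively it is about 82% to 83% under a Wald-type analysis whose true error is 3.0% to 3.2% at the design null and 4.1% to 4.2% if TAMIS recurrence is 3%.

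This rests on the stated rates, the 6-point margin, 83 assessable patients per arm, and the inference that a large-sample formula was used. The 73% is an unstratified figure; a stratified score interval was not evaluated separately, and it is assumed to behave similarly.

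**What to change.** Keep 198 patients. In the Sample size calculation and Data-analysis sections, name a score-type interval for the primary risk difference; a stratified Miettinen-Nurminen interval would fit the planned stratified analysis. Restate the power as about 73% with 166 evaluable patients under 3% and 6%. Add as sensitivity that it falls to about 32% if both rates are 6% and about 44% if both are 3%. Confirm the figure for the stratified interval once the strata are fixed.

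Reconcile the 6% and 3% margins as a separate step, and recompute the power if the margin changes.

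The cost is a change of wording and a less favourable stated power; no further patients are needed. For comparison, recovering 80% with a score test would take about 98 evaluable patients per arm: 196 / 0.84 = 233.3, or 234 randomised instead of 198.
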